### Setting

This study will be conducted in health centers affiliated to Tehran University of Medical Sciences. Tehran University of Medical Sciences covers primary health care services of 5 out of 22 districts of Tehran City (district numbers 10, 11, 16, 17 and 19) [21]. These health centers were chosen because they cover a significant portion of breastfeeding mothers of South Tehran, who usually bring their infants to theses\ health centers for vaccination, screening or growth monitoring. However, we will include four of these districts in our study (district numbers 10, 11, 16 and 17) because the health centers of district number 19 do not have the equipment for holding in-person classes and the population of Iranian breastfeeding mothers in that district is limited. These four districts have a total of 20 health centers. From among all these health centers, we will choose eight centers using simple randomization method; then, a cluster of four centers will be randomly selected for collecting the intervention group and four centers for collecting the control group. We will recruit eight to nine participants from each health center.

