### Recruitment

Eligibility for the study is as follows: being breastfeeding mothers who are within one year after giving birth and have sufficient breast milk for their own baby, with the approval of a doctor or midwife, having no serious medical condition (both mother and infant), and being a resident of Tehran.

The exclusion criteria are: breastfeeding cessation, loss of baby, not participating in more than one session of educational program, and not responding to more than 20% of the questionnaire.

Breastfeeding mothers who meet the inclusion criteria will be selected by convenience sampling, and they will be approached to explain the study aims, risks and benefits in a way that is easily understood. If they give permission to participate in study, they will provide written informed consent, then they will fill out the pretest questionnaire in order to obtain the baseline assessment.

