### Intervention design

Following baseline data collection, the intervention group will start receiving 60-minute weekly educational intervention based on TPB components for four weeks (Table 1).

**Table 1 Tab1:** The content of the educational sessions based on the theory of planned behavior

Session	Main purpose	Educational materials	Educational methods and time schedule
1	Improving breastfeeding mothers’ knowledge and attitudes toward DHM and HMB	• PowerPoint presentation • Booklet (including contents of all sessions) • Pamphlet of the first session	1) Introducing presenter and participants and explaining study aims (10 min) 2) Giving information on importance and background of breast milk donation and HMBs (40 min) 3) Question and answer (10 min)
2	Addressing the role of subjective norms in breast milk donation	• PowerPoint presentation • Pamphlet of the second session	1) Reviewing previous session (5 min) 2) Giving information related to Islamic laws of milk donation (15 min) 3) Presenter will use the psychodrama method. In this method two volunteer breastfeeding mothers role-play problems and release their intense emotions in regard to milk donation, then the presenter will guide their subjective norms [26] (30 min) 4) Question and answer (10 min)
3	Addressing the role of perceived behavioral control in breast milk donation behavior	• PowerPoint presentation • Pamphlet of the third session • Video	1) Reviewing previous session (5 min) 2) Giving information on requirements for breast milk donation, indication and contraindication of breast milk donation, process and cost of HMBs and current status of HMBs in Tehran (40 min) 3) Screening a video which shows how a HMB works (5 min) 4) Question and answer (10 min)
4	Addressing the behavioral intention and explaining how to implement the behavior of donating breast milk	• PowerPoint • Pamphlet of the fourth session • Video • Breast pump	1) Reviewing previous session (5 min) 2) Giving information on breast milk expression (10 min) 3) Showing how to express breast milk by hand and breast pump (25 min) 4) Showing videos of successful breast milk expression (10 min) 5) Question and answer (10 min)

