Lectures, small groups discussion, educational pamphlets and booklet, PowerPoint presentations, showing videos and pictures, will be the main educational methods and materials that we are going to use in order to make the program effective and interesting. Moreover, we will ask mothers to share the booklet and pamphlets with their family and friends. Sessions will be held in health centers for the intervention group while the control group will receive only usual education.

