### Data collection

The questionnaire will be uploaded to Porsline, a well-known online survey platform in Iran, to create a link for the questionnaire. Participants can use their mobile phones to open the link and fill out the questionnaire. A baseline assessment will be conducted prior to the intervention for both the intervention and control groups. In order to assess the immediate and long-term effects of the intervention prospectively, the first follow up assessment will be conducted immediately after the intervention, and the final one will be conducted 12 weeks later. Our primary outcomes are the number of mothers who have donated their breast milk and changes that have happened in breastfeeding mothers’ knowledge, attitudes, subjective norms, perceived behavioral control about DHM and intention to donate milk. Our secondary outcomes are the associations of behavioral determinants and social demographic variables with milk donation.

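### The session-attendance exclusion acts after allocation and can remove mothers from the intervention arm only, which is likely to favour the program

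*Protocol article*

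**What the plan says.** The Recruitment section of the protocol article opens its exclusion list with "The exclusion criteria are: breastfeeding cessation, loss of baby" and completes it with "not participating in more than one session of educational program, and not responding to more than 20% of the questionnaire". The entry condition is "being breastfeeding mothers who are within one year after giving birth and have sufficient breast milk for their own baby", so a woman who has already stopped breastfeeding would never have been enrolled.

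On allocation, the Setting section states that "a cluster of four centers will be randomly selected for collecting the intervention group and four centers for collecting the control group". On the sessions, Intervention design states: "Following baseline data collection, the intervention group will start receiving 60-minute weekly educational intervention based on TPB components for four weeks". The same section fixes who attends: "Sessions will be held in health centers for the intervention group while the control group will receive only usual education". On follow-up, Data collection states that "the first follow up assessment will be conducted immediately after the intervention, and the final one will be conducted 12 weeks later".

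Statistical analysis names repeated measures ANOVA, chi-square or Fisher's exact test, and logistic regression. Nowhere does the article say that mothers who meet an exclusion rule are still followed or still analysed.

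**The concern.** A rule that depends on behaviour after allocation, and that can be met in one arm only, selects mothers in that arm and leaves the other untouched by it. The intervention mothers who remain are those who kept coming. Willingness to attend four classes on milk donation is plausibly linked to willingness to donate, and both donation and intention to donate are primary outcomes. The Study design section says that the control group is there to separate the program's effect from other causes of an increase in donation. Motivation is one such cause, and the attendance rule lets it back into the comparison.

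The remaining rules raise a second, milder problem. Breastfeeding cessation and loss of the baby happen after enrolment in either arm. Cessation limits the ability to donate, yet the rule drops the mother from the group in which donors are counted.

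**Working it through.** **1. When each rule can be met, and in which arm**

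| Rule | Known when | Intervention | Control |
|---|---|---|---|
| Session attendance | During the four weekly sessions, after allocation and baseline | Yes | No (no sessions) |
| Breastfeeding cessation | After entry, which requires breastfeeding | Yes | Yes |
| Loss of baby | After entry | Yes | Yes |
| More than 20% of questionnaire unanswered | At the pretest or at follow-up; not stated | Yes | Yes |

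The attendance wording can mean missing two or more of the four sessions, or attending at most one. The first reading removes more mothers. Under either, the rule can reach any of the 33 intervention mothers and none of the 33 controls.

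**2. The plan's own figures (Sample size)**

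(1.96 + 1.64)² × (3.21² + 3.17²) / 3² = 12.96 × 20.353 / 9 = 29.3. The article prints 29.4; both round up to 30. Adding 10% gives 33 per group. The pooled SD is √(20.353 / 2) = 3.19. These figures are not disputed. The SD and the 3-point difference set the scale below.

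**3. Illustration for the scale outcomes, no true effect**

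These outcomes are changes from baseline, so what matters is the correlation ρ between attendance and change. Suppose the lowest fraction f of intervention mothers on attendance is removed. Under a normal model the mean of those kept shifts by

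bias = ρ × SD × φ(z_f) / (1 − f).

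Assumptions, none given in the documents: f = 10% (equal to the plan's attrition allowance) to 20%; ρ = 0.3 to 0.5; SD of change about 3.19.

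- f = 10%: φ(−1.282) / 0.9 = 0.195
- f = 20%: φ(−0.842) / 0.8 = 0.350

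| f | ρ | Bias (points) | Share of 3 points | Two-sided error at nominal 5% |
|---|---|---|---|---|
| 10% | 0.3 | 0.19 | 6% | 5.6% |
| 10% | 0.5 | 0.31 | 10% | 6.7% |
| 20% | 0.3 | 0.33 | 11% | 6.9% |
| 20% | 0.5 | 0.56 | 19% | 10.3% |

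The last column uses a standard error of 3.19 × √(1/33 + 1/(33(1 − f))) and ignores clustering.

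**4. Illustration for donation, no true effect**

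Assume 6 donors among 33 mothers in each arm (18.2%). If the attendance rule removes 3 intervention mothers and none is a donor, the rate becomes 6/30 = 20.0%. If it removes 6, it becomes 6/27 = 22.2%. Control stays at 18.2%. These are upper limits for those removals. If those removed donate at the same rate as the rest, nothing shifts.

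Cessation can move the rate either way. Dropping one mother who had not donated gives 6/32 = 18.8%; dropping one who donated before stopping gives 5/32 = 15.6%.

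**The case against.** The strongest reply is that a separate analysis plan may define the analysis sets, and that an article need not. That would answer a gap, but here the article states a rule that removes mothers. A plan that kept them would contradict the Recruitment section.

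Other objections stand, and they limit the point.

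- A reader might infer that the plan compares compliant intervention mothers with all controls. It does not: three of the four rules can remove controls too, and the direction of any bias from those three is not established.
- A reader might infer that a mother who stops breastfeeding is simply a non-donor. She may have donated first, and the donation item in Table 2 looks back six months.
- The 20% non-response rule stands in the same section as the pretest and may be a baseline completeness check applied before any session. The attendance rule allows no such reading.
- The scale outcomes are changes. If attendance reflects only stable motivation, it raises baseline and follow-up alike, and the change is not shifted. The illustration therefore needs attendance to correlate with change itself.
- No document says why mothers miss sessions, so the direction is expected and not proven.

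**Conclusion.** The point holds for the attendance rule. As written, it excludes on an event after allocation and can act in the intervention arm only. This follows from the text and needs no outside figure. It should be corrected, because it makes the primary comparison selective.

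Bias toward the program is likely but not certain, and its size is unknown. Under the stated assumptions it is about 0.19-0.56 points, 6-19% of the planned 3-point difference, with a false-positive risk of about 5.6-10.3% in place of 5%. That does not support a claim that an ineffective program would usually be declared effective.

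Cessation and loss of the baby, and the 20% rule if applied after the pretest, are two-sided. They still condition on events after allocation, and dropping mothers who stop breastfeeding distorts the donation denominator.

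**What to change.** - Do not use attendance, breastfeeding cessation, loss of the baby or partial questionnaire response as grounds for removal from the primary analysis.
- Follow every enrolled mother who remains willing, by the existing online link, and analyse her in the arm of her center.
- Count any donation made before breastfeeding stopped, and count none after that point.
- Keep the completed scales of a partly answered questionnaire and treat the rest as missing data.
- Report attendance as adherence. Label any attendance-based analysis as a per-protocol sensitivity analysis, and state whether the threshold refers to sessions missed or sessions attended.

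The cost is a change of wording and a little more follow-up work; the planned 33 per group is unchanged. The estimated effect may be smaller than among attenders. The change should be made before follow-up ends, because data on mothers who are dropped and not followed may not be recoverable later.

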### Development of the measurement tool

Data will be measured by a 46-item researcher-made questionnaire. This instrument has been created by reviewing literature on milk donation and previous studies on TPB and consists of seven sections as described in Table 2.

**Table 2 Tab2:** Theory of planned behavior-based survey questions

Sections	Example of questions	Scale
Sociodemographic and perinatal characteristics	Age, education, milk and blood donation history, breastfeeding history, economic status, parity, mode of delivery, the gestational age, sex and age of infant, awareness of HMBs and the source of information of HMBs	-
Knowledge of DHM and HMBs	“What is a human milk bank?” “What is the best alternative to mothers’ own milk for feeding premature babies?” “What effects does pasteurization have on donor milk?” “In the hospital, which babies receive donor milk?” “Who is eligible to donate their breast milk?” “How is donor milk stored in the hospital?” “How long can donated breast milk be stored in the hospital?” “What effects has pasteurized donor milk on premature babies?” “What should mothers do before donating their breast milk?” “What are the characteristics of informal breast milk sharing in the community?”	Multiple-choice questions
Attitude toward DHM and HMBs	“It is pleasant for me to donate breast milk” “Feeding premature babies with donor milk is better than formula” “Donor milk can reduce the stress of mothers who can’t feed their babies with their own breast milk” “By donating breast milk to a milk bank, I can save a baby’s life” “Donating breast milk to the milk bank can reduce the incidence of serious gastrointestinal disease in infants” “Donor milk in milk banks is safe and healthy” “When I don’t have enough breast milk, it is better to use donor milk instead of formula to feed my baby” “Donor milk in a milk bank may carry viruses and spread disease” “Donor milk should be used widely in hospitalized infants who cannot be breastfed, if it is possible” “Donor milk can treat newborns who weigh less than normal” “I think mothers should be rewarded for donating their milk” “After pasteurization, the nutrients in milk are all destroyed, so it is better to feed baby with formula”	5-point Likert (from strongly agree to strongly disagree)

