Subjective norms about DHM and HMBs	“My husband’s opinion on donating milk to the milk bank is important to me” “I will not donate my breast milk to the milk bank if my husband disagrees” “Opinions of people around me like my mother, family, friends etc. on donating milk are important to me” “I will not donate my milk to the milk bank if people around me (like my mother, family, friends etc.) disagree” “Milk donation and using donor milk have ethical issues in Islam” “God considers milk donation as a virtue and admirable action” “If I want to donate my milk, my family will support me”	5-point Likert (from strongly agree to strongly disagree)
Perceived behavioral control in milk donation	“I feel donating my milk will decrease my milk supply which is needed for my own baby” “It costs me a lot to donate my milk” “I can provide equipment for milk donation such as a container for storing milk, breast pump (if needed)” “I think I can be a milk donor” “If my husband or family are against donating milk, I can convince them” “I can express my breast milk correctly” “I can provide storage conditions for expressed milk”	5-point Likert (from always to never)
Intention to donate milk	“I am going to donate my milk to a milk bank within the next six months” “I am going to identify the milk banks where I live” “I am going to contact a milk bank within the next six months” “I am going to identify the nearest route to the milk bank” “I am going to undergo a pre-donation blood test” “I am going to inform other breastfeeding mothers about milk banks” “I am going to provide equipment for milk donation”	5-point Likert (from always to never)
Breastmilk donation	“I donated my breast milk in the last six months” “How many times did you donate your milk to the milk bank in the last six months?” “I will follow hygiene tips if I want to donate my breast milk”	Yes / No Number 5-point Likert (from always to never)

Theory of planned behavior assumes that individuals’ behavior is directly determined by three main components, namely: attitude, subjective norms, and perceived behavioral control [18, 19].

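### The 20% non-response limit is set on the pooled 46 items, so it can keep a mother with a primary outcome wholly blank and remove one whose other five are complete

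*Protocol article*

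**What the plan says.** The Recruitment section lists four exclusion criteria. The last is "not responding to more than 20% of the questionnaire". It sets no limit by section and requires no particular item to be answered.

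The section on the measurement tool says "Data will be measured by a 46-item researcher-made questionnaire", and that the instrument "consists of seven sections as described in Table 2". One of the seven sections is sociodemographic and has no response scale. The other six cover knowledge, attitude, subjective norms, perceived behavioral control, intention and donation.

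The Data collection section begins its list of outcomes with "Our primary outcomes are the number of mothers who have donated their breast milk" and adds changes in knowledge, attitudes, subjective norms, perceived behavioral control and intention. That makes six primary outcomes, each read from a different section of the one questionnaire.

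**The concern.** The completeness limit works at the level of the whole form, while the outcomes are analysed one at a time. A limit set that way can fail in two directions. It can keep a mother who has supplied nothing for one primary outcome. It can also remove a mother whose data are complete for every primary outcome but one, because of blanks that have no bearing on the rest.

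The second failure is the more costly. The Objectives section makes donation the main objective, and Table 2 measures it with a single Yes/No item. Losing a valid answer to that item because of blanks in the knowledge test wastes the trial's most important observation. The sample-size section plans 33 mothers per group against a requirement of 30, so each mother lost this way uses one of the three allowed for attrition (33 − 30 = 3).

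This point is about the level at which the threshold is set. Whether mothers may be excluded after allocation at all is a separate question.

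**Working it through.** **Inputs.** The 20% limit comes from Recruitment. The 46 items come from the measurement-tool section. The section sizes are counted from Table 2.

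**Reproducing the stated length.** The items printed in Table 2 are:

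- "Knowledge of DHM and HMBs": 10
- "Attitude toward DHM and HMBs": 12
- "Subjective norms about DHM and HMBs": 7
- "Perceived behavioral control in milk donation": 7
- Intention: 7
- Donation: 3 (the Yes/No item, the number of donations and a hygiene item)

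10 + 12 + 7 + 7 + 7 + 3 = 46, which matches the stated length exactly with the sociodemographic section left out. The column is headed as examples, but because the sum is exact the section sizes are secure.

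**Permitted blanks.** 0.20 × 46 = 9.2. Nine blanks (9/46 = 19.6%) do not exceed the limit. Ten (10/46 = 21.7%) do.

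**Each section left wholly blank, everything else answered:**

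| Left blank | Share of 46 | Result |
|---|---|---|
| Subjective norms (7) | 15.2% | kept |
| Perceived behavioral control (7) | 15.2% | kept |
| Intention (7) | 15.2% | kept |
| Donation section (3) | 6.5% | kept |
| Donation Yes/No alone (1) | 2.2% | kept |
| Knowledge (10) | 21.7% | excluded |
| Attitude (12) | 26.1% | excluded |

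Three of the five primary scales, and the donation item, can therefore be entirely missing in a mother who is kept. In the knowledge row the excluded mother has answered 36 of 46 items, including the donation question and all of the other four scales.

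**Sensitivity to the denominator (assumption).** Suppose about 12 to 14 sociodemographic items were also counted, giving 58 to 60 items.

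- At 58 items: 0.20 × 58 = 11.6, so 11 blanks pass. A blank knowledge section (10/58 = 17.2%) would be kept and a blank attitude section (12/58 = 20.7%) excluded.
- At 60 items: 0.20 × 60 = 12, so 12 blanks pass. A blank attitude section (12/60 = 20.0%) would be kept as well.

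On this reading more scales could be wholly blank, and the knowledge-only exclusion would no longer arise. The exact match at 46 makes it the less likely reading.

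**The same tolerance applied within each scale:**

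- Knowledge: 0.20 × 10 = 2, so at most 2 blanks
- Attitude: 0.20 × 12 = 2.4, so at most 2 blanks
- Each 7-item scale: 0.20 × 7 = 1.4, so at most 1 blank

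No scale could then be wholly blank and still be scored.

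**The case against.** The strongest reply is that this is a criterion for excluding participants and not a scoring rule. It does not say that everyone who passes counts as complete for every outcome. A whole-form limit can coexist with a per-scale scoring rule, and item-level missing data are commonly left to an analysis plan that is not shown here. This reply stands as far as scoring goes: the absence of a scoring rule from the article is no fault. It does not answer the point about exclusion. That threshold is written in the article, and a later scoring rule cannot restore a mother it has already removed.

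Several stronger readings are tempting, and the documents do not support them.

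- A reader might infer that a blank donation answer will be counted as a non-donor. No text codes a blank as no.
- A reader might infer large errors in scale totals. If totals were sums of the answered items and a typical answer scored 4, then 9 blank attitude items would give 3 × 4 = 12 in place of 12 × 4 = 48, an error of 36 points. That rests on a scoring rule the article does not state. If the total is set to missing, there is no such error.
- Setting such a figure against the 3-point difference in the sample-size calculation adds nothing, because that difference is not tied to any named scale.
- A reader might infer that the rule protects no outcome, or that any scale may be blank. On 46 items it does exclude wholly blank knowledge and attitude sections.

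It is also fair to say that the article gives no expected frequency of blanks. Nor does it say whether the online form allows items to be skipped, or at which assessment the rule applies. Forced answers throughout would largely remove the problem, although a non-response criterion implies that blanks are expected.

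**Conclusion.** The point holds as a defect in a stated rule. On the 46-item denominator, up to 9 blanks are accepted. Subjective norms, perceived behavioral control or intention can each be wholly missing in a mother who is kept, and so can the donation answer. Ten blanks confined to the knowledge section remove her from all six primary outcomes, although five of them are complete.

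This rests on three things: the Table 2 count, the literal reading of the limit as covering the whole form, and an online form that allows blanks. The loss of follow-up answers also requires the rule to be applied after baseline. The article does not say so, but a neighbouring criterion on missed sessions can only be judged once the program is under way. How often either failure would occur cannot be estimated from the article, and any error in points on a scale would be illustrative only. The rule should be changed, but nothing here shows that the trial's results would be materially biased.

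**What to change.** Replace the questionnaire-level exclusion with the same 20% tolerance inside each scale: at most 2 of 10 knowledge items blank, 2 of 12 attitude items, and 1 of 7 for subjective norms, perceived behavioral control and intention. Where a scale fails, set only that scale to missing at that assessment. Keep the mother in every outcome she did answer.

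Make the donation Yes/No a required field in the online form, and treat any blank that still occurs as missing.

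For the Likert scales, one or two permitted blanks may be prorated from the mean of the answered items. Choose the handling of blank knowledge items separately and state it, because a blank there may mean that the mother does not know, and prorating could then inflate her score.

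The cost is a short change to the protocol text, a scoring rule and one form setting, with no extra mothers or visits. The downsides are small: one mandatory field, and a slightly different number of mothers analysed for each outcome, which should be reported.

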## Methods

### Study design

A cluster randomized controlled trial will be carried out on breastfeeding mothers referred to health centers affiliated to Tehran University of Medical Sciences. A cluster randomized controlled trial design was chosen because it makes it easier for mothers to attend classes at their local health center, and in this design, the phenomenon of contamination between the intervention and control groups is avoided. Besides, it can help us increase the representativeness and generalizability of our study population and results. The control group allows us to analyze the direct effect of the intervention and discount an increase in milk donation due to other factors [20]. This study was approved by the Research Ethics Committees of School of Nursing and Midwifery & Rehabilitation - Tehran University of Medical Sciences (IR.TUMS.FNM.REC.1401.150).

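### Centers are allocated before mothers are chosen by convenience, consented and measured at baseline, with no concealment described, so selective recruitment may tilt the arms from the start

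*Protocol article*

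**What the plan says.** Under Setting, the protocol article draws eight of 20 health centers by simple randomization and then assigns them: "a cluster of four centers will be randomly selected for collecting the intervention group and four centers for collecting the control group". The next sentence reads: "We will recruit eight to nine participants from each health center".

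Under Recruitment, eligibility includes a judgment made by clinical staff, that mothers "have sufficient breast milk for their own baby, with the approval of a doctor or midwife". The choice of mother is described as follows: "Breastfeeding mothers who meet the inclusion criteria will be selected by convenience sampling". Of these mothers, "they will be approached to explain the study aims, risks and benefits in a way that is easily understood", and if they agree, "they will provide written informed consent, then they will fill out the pretest questionnaire in order to obtain the baseline assessment".

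Under Intervention design, the arms differ visibly at center level: "Sessions will be held in health centers for the intervention group while the control group will receive only usual education". The intervention is one 60-minute class a week for four weeks.

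Under Data collection, the primary outcomes are the number of mothers who have donated and the changes in knowledge, attitudes, subjective norms, perceived behavioral control and intention.

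**The concern.** In a cluster trial, randomization balances the centers in expectation. It balances the mothers only if the way they enter the study does not depend on the center's arm. Here the arm is set first, and the people are then chosen by a method that leaves room for discretion.

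The trait most likely to affect joining is openness to milk donation, and that is close to what every primary outcome measures. If intervention centers enroll more willing mothers, the arms differ in attitude, intention and likelihood of donating before the first class. A difference at follow-up could then be credited to the education when it came from recruitment.

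**Working it through.** **Order of steps, from the text**

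1. Eight centers are chosen and four are drawn for each arm (Setting).
2. Eight to nine mothers are recruited per center (Setting); 66/8 = 8.25.
3. Mothers are chosen by convenience, and aims, risks and benefits are explained (Recruitment).
4. Consent is given, then the pretest is completed (Recruitment).

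Centers are drawn for the purpose of collecting one group or the other, so step 1 precedes steps 2 to 4. Each center has one arm, and classes are held only for the intervention group. That recruiters and mothers know the arm is therefore an inference, though a strong one.

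**What the pretest can and cannot do**

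Let *b* be an entry difference between arms in a questionnaire score, with no true effect.

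- If the difference is stable, the expected baseline difference is *b* and the expected follow-up difference is *b*. The expected difference in change is *b* − *b* = 0, so analysis of change removes it.
- If openness to donation also affects how far a mother's score moves, the cancellation is incomplete.
- The number of mothers who donated after the program is not a change score. Baseline scores can be used to adjust it, but only for the part of willingness that the questionnaire captures.

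**The plan's own figure**

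Inputs (Sample size): SDs 3.21 and 3.17, difference 3 points, z values 1.96 and 1.64.

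n = (1.96 + 1.64)² × (3.21² + 3.17²) / 3² = 29.3, which rounds up to 30 (the article prints 29.4, also rounded to 30). Adding 10% gives 33 per group and 66 in total. The stated size reproduces and this point does not change it.

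**Illustration of size**

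The documents give no figure for an entry difference. I assume 0.2 to 0.3 SD.

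- Common SD = √((3.21² + 3.17²)/2) = 3.19.
- Shift in points: 0.2 × 3.19 = 0.64; 0.3 × 3.19 = 0.96.
- Share of the planned difference: 0.64/3 = 21%; 0.96/3 = 32%.
- Noncentrality with 33 per arm: 0.2 × √(33/2) = 0.81; 0.3 × √(33/2) = 1.22.

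Probability that a two-sided 5% test comparing follow-up means rejects when there is no true effect, ignoring clustering:

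| Assumed entry difference | 33 per arm, t test | 33 per arm, normal approximation | 30 per arm, t test |
|---|---|---|---|
| 0.1 SD | 6.9% | 6.9% | 6.7% |
| 0.2 SD | 12.6% | 12.8% | 11.9% |
| 0.3 SD | 22.5% | 23.0% | 20.8% |

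These figures describe an unadjusted follow-up comparison. They do not estimate the error rate of the planned repeated measures ANOVA.

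**The case against.** **Knowledge of the arm is not stated.** No sentence says who recruits, whether that person knows the center's arm, or when the allocation is disclosed, and a condensed article may leave such detail to the full protocol. This stands as a limit on wording: the arm can be expected to be known, but the documents do not show that it is. It does not remove the point, because the order of allocation and the convenience selection are both stated outright.

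**Consent content is not described by arm.** A reader might infer that intervention mothers are asked to agree to four classes and control mothers only to questionnaires. Recruitment describes one approach for all mothers, and Intervention design shows only that the arms receive different things. The documents do not support a claim that the information differs.

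**Over-representation is not certain.** A reader might conclude that willing mothers will be over-represented in the intervention arm. The text supports only that they may be.

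**The planned analysis uses baseline.** The questionnaire outcomes are defined as changes and analyzed by repeated measures ANOVA, so a stable entry difference would largely cancel. This stands, and it is why the 13 to 22% must not be read as the trial's error rate. It does not carry over to the donation count.

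**Representativeness.** A reader might say that convenience sampling contradicts the Study design statement that "it can help us increase the representativeness and generalizability of our study population and results". That sentence is hedged and the centers are drawn at random from 20 across four districts. Convenience choice limits generalizability but does not contradict the sentence, and does not by itself bias the comparison between arms.

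**Conclusion.** The concern holds as a weakness of sequence and selection. As written, allocation comes before convenience selection, consent and baseline, and nothing described keeps the arm from influencing who joins. The groups may therefore differ at entry on the trait the trial aims to change.

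For the questionnaire scores, the pretest and the analysis of change give partial protection. For the number of mothers who donated, protection is weaker, and the documents give no basis for a figure.

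The illustrative 13 to 22% rests on an assumed shift of 0.2 to 0.3 SD, 33 mothers per arm, no true effect, no allowance for clustering and no use of baseline. At 0.1 SD it would be under 7%. The change should be made before recruitment starts, since analysis can repair the problem only in part.

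**What to change.** Reverse the order of allocation and enrollment:

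- In all eight centers, approach consecutive eligible mothers at their routine visits for vaccination, screening or growth monitoring, instead of choosing by convenience.
- Use one common information sheet in every center, covering both possible arms.
- Complete consent and the baseline questionnaire for all eight to nine mothers in every center.
- Only then draw and disclose the 4:4 allocation, once, for all eight centers together. Disclosing center by center would make the later allocations predictable: once four centers are known to be in one arm, the rest are determined.

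The cost is modest. No extra participants are needed, only a reordering of steps and one information sheet. The downside is a wait between baseline and session 1 until the slowest center has enrolled, during which a few mothers may stop breastfeeding and so meet an exclusion criterion.
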